### Interim analyses {21b}

An interim analysis will be conducted when 122 clusters (50% of the planned number of clusters under the revised sample size calculation) have been followed-up for the primary outcome, adjusting the significance level according to Haybittle and Peto [74]. The Data Safety and Monitoring Committee will make recommendations at this point regarding whether to continue the trial as is or stop the trial for futility, with consideration of studying an alternative promising agent as COVID-19 PEP or otherwise altering the study intervention as applicable. The final decision regarding stopping or continuing the trial will rest with the Co-Principal Investigators, in consultation with the Steering Committee.

### Methods for additional analyses (e.g., subgroup analyses) {20b}

Subgroup analyses of the primary outcome will be performed according to the type of exposed contact (e.g., healthcare workers, household members) since prior data have suggested considerably different secondary attack rates for respiratory viruses in these settings; according to the number of days between exposure and enrollment, since PEP is most likely to be effective when started as soon as possible after exposure; and according to site/city, since small differences related to practice patterns and other unknown factors may exist.

### Methods in analysis to handle protocol non-adherence and any statistical methods to handle missing data {20c}

The primary analyses will be by intention-to-treat. Missing data will be imputed (e.g., regression, interpolation) under a variety of assumptions (e.g., missing at random, missing completely at random), and conduct sensitivity analyses to determine the robustness of our findings. Exploratory analyses will examine whether participants with greater adherence experience a lower risk of the primary outcome, using both self-report and pharmacokinetic methods (lopinavir levels in dried blood spots at day 14) to confirm adherence.

### Plans to give access to the full protocol, participant level-data and statistical code {31c}

The full study protocol is provided as an Appendix to this article. After the primary and secondary analyses have been completed, de-identified data will be uploaded to a public data repository (e.g., Dryad).

## Oversight and monitoring

### Composition of the coordinating center and trial steering committee {5d}

Day-to-day operations of the trial will be overseen by an experienced Project Manager at the lead site. The Steering Committee is composed of twelve individuals with expertise in infectious diseases, infection prevention and control, clinical trials, biostatistics, and medical microbiology, including the Co-Principal Investigators and Site Principal Investigators representing multiple cities.

Data management will be overseen by the Applied Health Research Centre at the Li Ka Shing Knowledge Institute of Unity Health Toronto, whose experienced project managers, research assistants, database developers, data managers, programmers, statistical team, and information technology staff currently support over 50 CIHR and NIH-supported clinical trials, registries, and observational studies.

### Composition of the data safety monitoring board, its role and reporting structure {21a}

The DSMC is an independent group of four individuals with expertise in clinical trials, infectious diseases, and biostatistics, appointed by and advisory to the Steering Committee. The DSMC will remain standing until the end of trial accrual. All DSMC members are expected to remain free from perceived or actual conflict of interest throughout their involvement in the trial and will be asked to complete a conflict of interest form at the start of their involvement in the DSMC. The DSMC Charter is posted at the study website (www.optionslab.ca/projects/coriprev) and is a living document that may be revised at regular intervals if needed.

Of note, the World Health Organization has established a process to promote data-sharing between individual clinical trials of COVID-19 pre-exposure prophylaxis, PEP, and treatment globally. After each review meeting, the CORIPREV-LR DSMB will confidentially share its closed report with DSMCs monitoring other, closely related clinical trials; the DSMCs for these other trials will do the same. This process will enhance the ability of each DSMC to provide optimal oversight to the individual trials regarding safety and efficacy without jeopardizing the integrity of each trial.

### Adverse event reporting and harms {22}

An adverse event (AE) is defined as any untoward medical occurrence in a patient or clinical investigation participant, administered a study medication/intervention, which does not necessarily have a causal relationship with this treatment. An AE can therefore be any unfavorable and unintended sign (including an abnormal laboratory finding), symptom, or disease temporally associated with the use of a medicinal (investigational) study medication/intervention, whether or not related to the medicinal (investigational) study medication/intervention.

During each follow-up visit with the participant, information on AEs will be gathered by study coordinators using open-ended questions about any untoward medical occurrences and documented accordingly. AEs will be graded as mild, moderate, severe, or life-threatening according to the DAIDS Table for Grading the Severity of Adverse Events [28] and assessed for causality as probably related, possibly related, unlikely to be related or not related to the study drug (investigational arm only). Data will be reported on AEs of any grade, whether expected or unexpected, regardless of causality assessment.

Serious adverse events (SAEs) are defined as AEs that are life-threatening; result in death, hospitalization, or prolongation of existing hospitalization; or result in significant disability or a congenital anomaly, with the exception of developing COVID-19, which will be captured as an outcome instead. SAEs must be reported to the Project Manager within 24 h of the site becoming aware of the event; the Project Manager will ensure prompt reporting to regulatory authorities.

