### Strategies to improve adherence to interventions {11c}

Participants in the active arm of the trial will receive a few doses of dimenhydrinate 50 mg (for management of nausea) and loperamide 2 mg (for diarrhea) in their study kits, in order to help manage potential gastrointestinal side effects of the study drug.

Of note, the study team considered a loading dose of LPV/r at baseline (400/100 mg four times on day 1, followed by twice daily to complete 14 days total) in order to optimize the pharmacokinetics of this drug against SARS-CoV-2. However, this strategy was not selected due to concern that it may be associated with an increased risk of side effects that could compromise further adherence with the study drug.

Adherence will be monitored in two ways. First, participants in the active arm will be asked to complete a daily electronic symptom diary which asks whether each dose was early, on time (within 3 h), late, or forgotten/missed. Second, a random ~ 30% subset of participants in the active arm will have a self-collected dried blood spot collected at day 14 for testing of plasma lopinavir levels as a biomarker of adherence and to assess for a pharmacokinetic correlate of protection. Because these levels can be affected by hematocrit [42, 43], this subset of participants will also undergo a complete blood count at the day 35 in-person visit, together with the routine blood draw for serology.

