Adverse events: the proportion of participants exhibiting adverse events of any grade as defined using the DAIDS Table for Grading the Severity of Adverse Events, at 7, 14, 35, and 90 days [28].Symptomatic microbiologically confirmed SARS-CoV-2 infection: proportion of participants with fever, cough, or other respiratory/systemic symptoms (including but not limited to fatigue, myalgias, arthralgias, shortness of breath, sore throat, headache, chills, coryza, nausea, vomiting, diarrhea), combined with microbiologic confirmation of SARS-CoV-2 infection by PCR, by day 14.Seropositivity: proportion of participants with reactive serology at day 35.Days of hospitalization attributable to COVID-19 disease: The median number of days (or partial days) spent admitted to an acute care hospital will be tabulated both at day 35 and day 90.Respiratory failure requiring ventilatory support attributable to COVID-19 disease: The median number of days (or partial days) requiring (i) non-invasive or (ii) invasive ventilation will be tabulated both at day 35 and day 90.Mortality (proportion of participants who die) attributable to COVID-19 disease and all-cause mortality will be tabulated at 35 and 90 days.Short-term psychological impact of exposure to COVID-19 will be measured at day 14 using the K10, a validated measure of non-specific psychological distress, with results aggregated as the proportion with a score of ≥ 16 [45, 46].Long-term psychological impact of exposure to COVID-19 will be measured at day 90 using the Impact of Event Scale, a validated measure of traumatic stress response, with results aggregated as the proportion with a score of ≥ 26 [47, 48].Health-related quality of life will be measured using the EQ-5D-5L (EuroQol-5D) (https://euroqol.org/eq-5d-instruments/eq-5d-5l-about/). The EQ-5D consists of two pages: the EQ-5D descriptive system and the EQ visual analog scale (EQ VAS). The descriptive system comprises five dimensions: mobility, self-care, usual activities, pain/discomfort and anxiety/depression. The tool will be administered to participants at 1, 14, 35 and 90 days; the primary interest is in the median index value at 14 days.

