^d^An additional swab is to be collected within 24 h if symptoms develop before day 14. Two respiratory specimens (swabs, saliva, etc.) are to be taken at day 14 timepoint, unless an extra swab was already taken due to the development of symptoms in which case only one is collected

*NB:* other respiratory specimen(s) may be collected depending on availability of supplies

^e^The dried blood spot at baseline is to be performed in participants in the active arm only (since these participants are already collecting a drop of blood for the HIV self-test), for SARS-CoV-2 serology

^f^The dried blood spot at day 14 is to be performed in a random subsample of participants in the active arm only, for lopinavir levels. These participants are the only ones that require a CBC at day 35 since the hematocrit is required for interpretation of DBS lopinavir levels [42, 43]

^g^Baseline serology is to be collected at baseline only if the participant is institutionalized

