## Statistical methods

### Statistical methods for primary and secondary outcomes {20a}

The primary outcome is microbiologically confirmed SARS-CoV-2 infection, i.e., detection of viral RNA in a respiratory specimen (oropharyngeal/nasal swab, nasopharyngeal swab, sputum specimen, saliva specimen, oral swab, endotracheal aspirate, bronchoalveolar lavage specimen) by day 14. Our primary analysis will be a generalized linear mixed model (GLMM) with logit link to estimate the effect of LPV/r on the probability of infection while accounting for clustering of participants in rings, with stratification by the randomizing site. The primary analysis will be unadjusted; in addition, multivariable models will adjust for key characteristics of both contacts (age, sex, co-morbidity, exposure characteristics such as type, duration, and timing) and index cases (illness severity, concomitant medications, etc.). In particular, we will include sex/gender-based analyses with variables specific to contacts and types of exposures. Participants with specimens positive for SARS-CoV-2 at baseline will be permitted to continue in the trial and follow all study procedures, including completion of the 14-day course of study drug for those in the active arm, as noted in section 12.2.2. These participants will be excluded from the primary and secondary analyses regarding LPV/r as PEP, but included in secondary analyses regarding early LPV/r treatment, as noted below.

To assess safety, adverse events will be tabulated according to grade and causality assessment using definitions from the DAIDS Table for Grading the Severity of Adverse Events [28], and compared between study arms.

As for the primary analysis outlined above, GLMM with logit link (for dichotomous outcomes) or identity link (for continuous outcomes) will also be used to compare the following secondary outcomes between study arms:

Symptomatic COVID-19 disease by day 14Seropositivity by day 35Days of hospitalization attributable to COVID-19 disease by day 90Respiratory failure attributable to COVID-19 disease requiring (i) non-invasive and (ii) invasive ventilation by day 90Mortality attributable to COVID-19 diseaseShort-term psychological distress, defined as scoring ≥ 16 on the K10 [45, 46] at day 14Long-term traumatic stress response, defined as scoring ≥ 26 on the IES scale [47, 48] at day 90Health-related quality of life, measured by the EQ-5D-5 L on days 1, 14, 35, and 90

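### The only scheduled blood count is in about 30% of the LPV/r arm at day 35, and nothing keeps its abnormalities out of the between-arm adverse event comparison

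*Protocol article*

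**What the plan says.** **Who is tested.** Under strategies to improve adherence {11c}, "a random ~ 30% subset of participants in the active arm will have a self-collected dried blood spot collected at day 14", and "this subset of participants will also undergo a complete blood count at the day 35 in-person visit". Note f to Table 1 (Participant timeline {13}) adds: "These participants are the only ones that require a CBC at day 35", and gives the reason: "since the hematocrit is required for interpretation of DBS lopinavir levels". The CBC row of Table 1 has a single entry, which carries that note. No CBC is scheduled at baseline or in the control arm.

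**What counts as an event.** Adverse event reporting and harms {22} includes laboratory findings: "An AE can therefore be any unfavorable and unintended sign (including an abnormal laboratory finding), symptom, or disease temporally associated with the use". Events of every grade are reported, whatever the causality assessment. The same section says that coordinators collect events at follow-up visits by open-ended questioning.

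**What is compared.** Outcomes {12} lists "the proportion of participants exhibiting adverse events of any grade as defined using the DAIDS Table for Grading the Severity of Adverse Events" as a secondary outcome at days 7, 14, 35 and 90. Under the statistical methods {20a}, adverse events are tabulated by grade and causality "and compared between study arms".

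**The concern.** A between-arm comparison of adverse events is interpretable only if events have the same chance of being found in both arms. Here the definition admits laboratory abnormalities, and neither grade nor causality screens out a mild incidental one. The one scheduled test that would reveal a haematological abnormality is done only in LPV/r participants, for a pharmacokinetic reason.

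Without a baseline count, a long-standing mild anaemia or low white count first seen at day 35 cannot be told from a new one. A control with the same blood picture has no scheduled test that would show it.

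If such findings are recorded, the LPV/r event proportion rises for a reason unrelated to the drug. If some sites record them and others do not, the coding is inconsistent as well. Randomisation does not help, because the difference lies in the testing schedule and not in the participants.

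**Working it through.** **Step 1: arm size.** The sample size section {14} and the abstract give 15% against 9% (a 40% relative reduction), 80% power, alpha 0.05 (taken as two-sided), ring size 5 and ICC 0.05.

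- The two-proportion formula gives 460 per arm.
- Design effect = 1 + (5 − 1) × 0.05 = 1.2, and 460 × 1.2 = 552.
- 552 / 5 = 110.4 clusters per arm, which reproduces the stated 110.
- 110.4 × 1.1 = 121.4, rounded up to 122 rings per arm. That is 244 rings, 1220 participants and 610 per arm, as the article states.

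**Step 2: how many are tested.** 0.30 × 610 = 183 LPV/r participants. After 10% loss, with about 550 per arm, 0.30 × 550 = 165. Controls: 0.

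**Step 3: size of the possible distortion.** Two inputs are missing from the documents and are assumed here:

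- q, the share of CBCs with an abnormality that is recorded as an adverse event;
- b, the share of participants with any other adverse event, equal in both arms.

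A CBC finding changes the any-event proportion only in someone without another event. So the added LPV/r proportion = 0.30 × q × (1 − b). In percentage points:

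| q | b = 10% | b = 30% | b = 50% |
|---|---|---|---|
| 2% | 0.54 | 0.42 | 0.30 |
| 5% | 1.35 | 1.05 | 0.75 |
| 10% | 2.70 | 2.10 | 1.50 |
| 20% | 5.40 | 4.20 | 3.00 |

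For example, 0.30 × 0.05 × 0.50 = 0.0075 and 0.30 × 0.10 × 0.90 = 0.027.

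**Step 4: what this would do to a test.** The article names no test for adverse events, so this is illustrative. Take a two-sided 5% comparison of proportions, no true difference and an effective 610 / 1.2 ≈ 508 per arm. The chance of a result favouring control is nominally 2.5%. For q = 5–10% it becomes about 10–27% if b = 10%, and about 4–7% if b = 50%.

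**Step 5: haematology tabulated alone.** The expected number of recorded abnormalities from the scheduled CBC is 183 × q, or about 9 to 18 for q = 5–10% (165 × q, about 8 to 17, after loss). Controls have no scheduled CBC and so contribute none. Whatever the value of q, any excess from this source is pure ascertainment.

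**The case against.** The strongest reply is that the link from CBC to adverse event is never made. The article gives one collection route, open-ended questioning at visits, and it is the same in both arms. The definition says what an event can be; it does not tell anyone to grade every out-of-range value from a pharmacokinetic sample. A reader might infer that LPV/r participants will accumulate haematology events that controls cannot have, or that the comparison is biased by design. The documents do not support either reading. No section says that CBC results are reviewed, graded or entered as events, and controls can report abnormalities found in clinical care. They lack only a scheduled test.

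Other parts of the reply also stand. Days 7 and 14, which cover the dosing period, are untouched. The sizes above rest on assumed rates and on every abnormality being recorded, so they are upper bounds for each assumed rate. The no-difference scenario in step 4 is artificial, because the article itself expects gastrointestinal side effects on LPV/r. The outcome is secondary, and the efficacy outcomes are not involved.

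It can also be said that the full protocol or the analysis plan, neither shown, may settle how incidental results are handled. That may be so. But the article itself fixes the testing schedule, the event definition and the comparison, and taken together they allow the asymmetry. Open-ended questioning describes how information is gathered; the definition decides what qualifies, and it names laboratory findings. A site holding an abnormal count has grounds in the text to record it.

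**Conclusion.** The concern holds as a risk created by the definition and the schedule together. Any abnormality from the day-35 CBC that is recorded as an adverse event counts only towards LPV/r, at days 35 and 90, with neither a baseline value nor a scheduled control test to set against it.

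Assuming that 5–10% of CBCs are abnormal and all are recorded, the spurious any-event difference is at most about 0.75–2.7 points, for 50% down to 10% of participants having another event. It is zero if no CBC result is recorded. In a haematology tabulation, any excess from the scheduled CBC would be an artefact of testing at every assumed rate. Severity is minor.

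**What to change.** In the statistical methods {20a} and in adverse event reporting {22}, state that the between-arm comparison uses only events ascertained the same way in both arms. Flag each adverse event by source. List abnormalities found only on the day-35 CBC descriptively, for the tested LPV/r subset, outside the any-event proportion and any between-arm comparison. Clinical follow-up and regulatory reporting of these results stay unchanged. If the full protocol or analysis plan already has such a rule, a cross-reference is enough.

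The cost is one sentence and a source flag, with no new tests, visits or participants. The downside is that CBC findings are described and not compared; with no control counterpart, that comparison could not be valid anyway.

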### Provisions for post-trial care {30}

This study will provide access to 14 days of the study drug for those randomized to the intervention arm only. Because a secondary objective of the trial is to examine the impact of LPV/r on clinical outcomes in those who test positive for SARS-CoV-2, the full course of study drug should be continued regardless of the results of COVID-19 testing.

In the event that a participant tests positive for SARS-CoV-2 during or after the follow-up period, efforts will be made to link the individual to ongoing clinical trials of COVID-19 treatment. However, no guarantee of access to investigational product can be made. At the time of writing, there are no known effective anti-viral treatments for established COVID-19 infection, although dexamethasone has been shown to improve 28-day mortality in hospitalized patients requiring oxygen or invasive mechanical ventilation [44].

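### The COVID-19 exception to the SAE definition has no stated reach, and the hospitalisation, mortality and adverse event comparisons need all-cause and COVID-free versions beside them.

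*Protocol article*

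**What the plan says.** All references are to the protocol article.

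- **SAE definition, Adverse event reporting and harms {22}.** An SAE is an AE that is life-threatening, leads to death, a new or prolonged hospital stay or significant disability, or is a congenital anomaly, "with the exception of developing COVID-19, which will be captured as an outcome instead". The expedited duty attaches to this class alone: "SAEs must be reported to the Project Manager within 24 h of the site becoming aware of the event".
- **AE definition, same section.** An AE includes "any unfavorable and unintended sign (including an abnormal laboratory finding), symptom, or disease temporally associated" with study treatment. COVID-19 is not excepted. Further, "Data will be reported on AEs of any grade, whether expected or unexpected, regardless of causality assessment". Relatedness to study drug is judged in the investigational arm only.
- **Outcomes {12}.** The proportion with an AE of any grade is a secondary outcome. The hospital outcome is "Days of hospitalization attributable to COVID-19 disease". For deaths, "Mortality (proportion of participants who die) attributable to COVID-19 disease and all-cause mortality will be tabulated at 35 and 90 days".
- **Statistical methods {20a}.** For safety, "adverse events will be tabulated according to grade and causality assessment" and compared between arms. The modelled list contains hospital days, ventilation and mortality, each only if attributable to COVID-19.
- **Objectives {7}.** Hospitalisation and mortality are listed without that restriction.
- **Who will be blinded {17a}.** Participants, coordinators and investigators know the allocation. Laboratory technologists and statisticians do not.
- **Provisions for post-trial care {30}.** In the LPV/r arm, "the full course of study drug should be continued regardless of the results of COVID-19 testing".

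**The concern.** Three separate problems arise where COVID-19 is both the study disease and a possible safety event.

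1. **Reach of the SAE exception.** A site facing a COVID-19 admission cannot tell from {22} whether a 24-hour report is due. This matters because infected participants stay on study drug and early treatment is a stated objective. In them, harm from the drug could look like worse COVID-19.
2. **Comparisons that depend on attribution.** Whether a hospital stay or death enters the model depends on its being judged due to COVID-19. If the people supplying that judgement know the arm, the comparison can shift by arm without any true difference. An all-cause comparison would be immune to this, but none is planned for hospitalisation, and for mortality it is tabulated and not modelled.
3. **Efficacy mixed into the toxicity comparison.** COVID-19 symptoms count as AEs. The symptom list in {12} includes nausea, vomiting and diarrhoea, the same gastrointestinal effects that the article expects from LPV/r. If the drug prevents infection, its arm has fewer such symptoms, and the any-grade AE comparison understates its toxicity.

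**Working it through.** The plan gives no figure for this point. The first two parts set the text side by side, and the third is arithmetic.

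**1. What the exception can mean.** Two readings are open.
- *Narrow:* only becoming infected is excepted. An uncomplicated infection meets none of the seriousness criteria, so the exception would remove almost nothing.
- *Broad:* COVID-19 that meets a seriousness criterion is excepted. The exception then has practical effect. It also fits the stated replacement, because COVID-19 hospital days, ventilation and death are all listed outcomes.

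The broad reading is the more natural, but the text does not state it. Under it, only the 24-hour route is lost. AE grades run up to life-threatening with no COVID-19 exception, and Plans for assessment {18a} collects hospitalisation, ventilation and mortality at interviews on days 7, 14, 35 and 90. Neither reading settles the position of participants positive at baseline, who already have the infection at enrolment.

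*Scale under the broad reading.* The planning inputs are 15% in controls, a 40% relative reduction and 1220 participants.
- LPV/r rate: 0.15 × (1 − 0.40) = 0.09.
- Per arm: 1220 / 2 = 610.
- Expected infections: 610 × 0.15 = 91.5 (control) and 610 × 0.09 = 54.9 (LPV/r). Without the 10% loss allowance, 110 clusters × 5 = 550 gives 82.5 and 49.5.
- The documents give no share of infections that become serious. Assuming 1% to 10%, the 610 base gives 0.9 to 9.2 serious events in controls and 0.5 to 5.5 on LPV/r (0.9 to 9.2 if the drug has no effect).

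**2. All-cause against attributable.**

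| Event | Attributable to COVID-19 | All-cause |
|---|---|---|
| Hospitalisation | Modelled ({20a}) | No comparison planned |
| Mortality | Modelled ({20a}) | Tabulated at days 35 and 90 ({12}) |

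A hospital stay unrelated to COVID-19 remains an SAE, so it is not lost. It is counted in a different place, and no planned comparison puts the two kinds together. The documents give no hospitalisation or misattribution rate, so the possible bias cannot be sized.

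**3. Offset in the any-grade AE proportion.** Let *s* be the share of infections with symptoms and *b* the share of participants spared a symptomatic infection who would have another AE anyway. Prevention then lowers the LPV/r arm's any-grade AE proportion by

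(0.15 − 0.09) × *s* × (1 − *b*).

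The documents give neither *s* nor *b*, so both are assumptions.
- *b* = 0: 0.06 × 0.5 = 3 points at *s* = 0.5, and 0.06 × 1.0 = 6 points at *s* = 1.0. This is the ceiling, because a participant counts once however many AEs occur.
- *b* = 0.5: 0.06 × 0.5 × 0.5 = 1.5 points, and 0.06 × 1.0 × 0.5 = 3 points.
- If the drug does not prevent infection, the difference in rates is zero and so is this offset.

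Tabulating by causality does not separate the two effects between arms, because the control arm has no causality assessment to set against it.

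**The case against.** The strongest reply is that capturing the study disease as an outcome, equally in both arms, is a legitimate design choice, and that the full protocol (Appendix A) and the DSMC charter, neither shown, may define the exception and how outcomes reach the committee. That stands as far as it goes. It is why the SAE part is put as wording to clarify and not as a missing safeguard. It does not answer the other two parts, which follow from rules that the article itself states.

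A reader might infer more than the documents support:

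- *That serious worsening on LPV/r leaves safety monitoring.* The text excepts developing the disease and does not name its serious consequences. Even on the broad reading, the events stay in the graded AE data and in the scheduled outcomes.
- *That such events surface only in tables at days 35 and 90.* They are also collected at days 7 and 14.
- *That baseline-positive participants are plainly exempted.* An exception for developing COVID-19 does not clearly reach people who already have it.
- *That unblinded site staff decide each attribution.* The article does not say who attributes a hospital stay or death, or whether this is adjudicated. It says only that participants, coordinators and investigators know the arm. Infection status itself rests on PCR read by blinded laboratory staff.
- *That DSMC review is confined to the single formal efficacy look.* The article speaks of a closed report after each review meeting and of oversight of both safety and efficacy.

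**Conclusion.** The point holds in three limited parts.

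1. The SAE exception is ambiguous about serious COVID-19. It does not state an exclusion. On its more natural reading the loss is the 24-hour route alone.
2. The modelled hospitalisation and mortality comparisons depend on attribution to COVID-19 in a trial open-label to those closest to the events. For hospitalisation no all-cause comparison is planned, although the objectives carry no such restriction. The size of any bias is unknown.
3. The any-grade AE comparison mixes efficacy with toxicity. The offset from prevented infections is at most 3 to 6 percentage points. This rests on the planning rates of 15% and 9% and an assumed 50% to 100% of infections being symptomatic. It shrinks with every participant who has another AE anyway and vanishes if the drug does not prevent infection.

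The primary outcome is untouched. The second and third parts are worth changing because they follow from stated rules and affect how the safety results will be read.

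**What to change.** - **Outcomes {12} and Statistical methods {20a}:** compare all-cause hospitalisation and all-cause mortality between arms beside the versions attributable to COVID-19. Report the AE proportion by arm twice, with and without COVID-19 symptoms in PCR-confirmed participants.
- **Adverse event reporting and harms {22}:** reword the exception so that it covers only the diagnosis of SARS-CoV-2 infection. Alternatively, keep it broader and state how and when serious COVID-19 events reach the DSMC. Apply the same rule to participants positive at baseline.

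The cost is a few more reports and one or two extra tables. AEs and hospitalisations are already collected at the scheduled interviews, and PCR results are already part of follow-up.
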